**Thematic block and examples of items**
Characteristics of the respective organization and knowledge of the interventionIn which organization do you work?How many permanent employees does your organization have?Adoption of the intervention and reasons for or against adoptionDid your organization participate in 10,000 Steps Duesseldorf?What contributed most to the decision to carry out 10,000 Steps Duesseldorf?What are the main reasons why 10,000 Steps Duesseldorf was not implemented?Implementation of the interventionHow many employees worked on the implementation of 10.000 Steps Düsseldorf?What was or is the total investment, excluding staff costs, for your organization to implement 10,000 Steps Duesseldorf?Did you distribute the program materials (stickers, brochures, flyers) of 10,000 Steps Duesseldorf?Which media channels did you use and at what cost?Long-term maintenance of the interventionDoes your organization intend to plan further intervention activities in the future following the past or current 10,000 Steps Duesseldorf activities?Why are no 10,000 steps Duesseldorf program activities planned for the future?

### Health Economic Evaluation

The health economic evaluation will include a cost-effectiveness analysis (CEA) and a cost-utility analysis from a societal perspective. An incremental cost-efficacy ratio (ICER; additional costs per additional person walking 10,000 steps/day) and an incremental cost-utility ratio (ICUR; additional cost for an additional QALY gained) will be determined. The outcome of the CEA is based on the primary outcome of the intervention and will be taken from the step counter measurement. QALYs will be calculated based on the EQ-5D-5L [44], which is a widely used standardized instrument to assess health-related quality of life. The EQ-5D-5L is evaluated using a German tariff to obtain preference weights [55]. As the intervention might influence people beyond health, we will also consider capability well-being using the ICEpop CAPability measure for adults (ICECAP-A) [48]. We will use a UK scoring tariff because a German tariff does not exist yet [56] and compare utilities based on capabilities with those based on QALYs.

The costs considered in the health economic evaluation comprise costs related to the development and provision of the intervention (eg, print-based materials, website, and time associated with the development of the intervention as opportunity costs), health care use (physician’s visits, contact with therapists, hospital stays, and rehabilitation), and costs associated with PA behavior (devices to support PA, membership fees [eg, gym membership], disability to work, and patient time). Productivity loss due to disability to work is calculated based on the human capital approach [57]. In a sensitivity analysis, patient time associated with PA, evaluated via opportunity costs, will also be examined. A discounting of costs and outcomes is not planned because of the short study duration.

The analysis will be performed according to the intention-to-treat principle. In the base case analysis, missing values will be imputed via multiple imputation. To make the random samples from the intervention and control region comparable, propensity score matching in the form of a weighted regression model will be applied after the imputation and for each imputed data set as suggested by Al-Janabi et al [58]. Covariates used for the matching will be the number of steps taken at baseline, age, gender, level of education, and household income.

Mean incremental costs and the mean incremental outcome of the CEA will be estimated by a using a Generalized Linear Model with gamma distribution and log link function. To estimate the mean incremental outcome of the CEA (an additional person who walks 10,000 steps/day), a Generalized Linear Model with binomial distribution and logit link function will be estimated. Bootstrap procedures will be used to calculate 95% significance intervals for the ICER and ICUR [59,60]. To investigate uncertainty surrounding the ICER and ICUR, cost-effectiveness and cost-utility planes will be generated [61,62].

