**Socioeconomic characteristics**				
	**NAKO^a^ core interview [34]**			
		Date of birth	T_0_^b^	
		Country of birth	T_0_	
		Country of birth outside of Germany	T_0_	
		Time since living in the territory of the Federal Republic of Germany or DDR	T_0_	
		Nationality (German vs other)	T_0_	
		Country of birth (father and mother)	T_0_	
		Marital status	T_0_	
		In a relationship	T_0_	
		Living together with partner	T_0_	
		Living district	T_0_	
		Type of residence	T_0_	
		Number of individuals living in the household	T_0_	
		Number of individuals in the household >14 years	T_0_	
		Highest education degree obtained	T_0_	
		Types of educational qualifications	T_0_	
		Other types of educational qualifications	T_0_	
		Employment status (eg, full time or part time or unemployed)	T_0_	
		Working hours per week	T_0_	
		Previous employment status (full time or part time)	T_0_	
		Occupation	T_0_	
		Income level	T_0_	
		Average net monthly income	T_0_	

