### Secondary Outcomes

Secondary outcomes assessed at baseline and follow-up in the telephone-administered interview are described in detail in Table 2.

Briefly, at the individual level, height and weight, general self-rated health, and health behavior (smoking status, fruits and vegetables consumption, and alcohol use) are assessed. In addition, the determinants of PA are assessed (eg, social support). At the environmental level, perceptions of characteristics of the physical environment relevant for engaging in PA are assessed. To assess knowledge and awareness of intervention messages and activities spread and implemented in the intervention city districts, self-generated items are included in the follow-up questionnaire. Study participants are also asked about health care use (physician’s visits, contacts with therapists, hospital stays, and rehabilitation) retrospectively for the previous 6 months and costs pertaining to devices bought to support engagement in PA or membership fees (eg, gym membership), as well as sick leave days.

**Table 2 table2:** Outcomes assessed in the telephone-administered interviews (part 2).

Instrument or scale and outcome				Time of assessment

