	**Modified version of the questionnaire of Chernyak et al [42]**			
		Have you seen a physician in the last 6 months?	T_0_, T_1_	
		Which physicians have you seen in the last 6 months? (eg, general practitioner, gastroenterologist, diabetologist)	T_0_, T_1_	
		How many contacts you had in each of the last 6 months and how much time you spent in total on your outpatient?	T_0_, T_1_	
		Have you been to a therapist (eg, psychotherapist, physical therapist, speech therapist) for treatment in the last 6 months?	T_0_, T_1_	
		Which therapists have you seen in the last 6 months?	T_0_, T_1_	
		How many treatment sessions have you had in each of the last 6 months? And what is the total amount of time you spent on your treatment sessions?	T_0_, T_1_	
		Have you been hospitalized for inpatient treatment in the last 6 months?	T_0_, T_1_	
		Please indicate the reason and duration of stay for each hospitalization.	T_0_, T_1_	
		Have you been to rehabilitation in the last 6 months?	T_0_, T_1_	
		Indicate for each stay whether it was outpatient or inpatient rehabilitation. Please indicate the duration of your stay.	T_0_, T_1_	
		Please indicate how many days in total.	T_0_, T_1_	
		If your sick leave has been for more than 6 months, please indicate how many days you have been on sick leave.	T_0_, T_1_	

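### Work status, hours and income are recorded only at baseline, so a follow-up report of no sick leave cannot separate people at work from those who have left it, although productivity loss is a costed outcome

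*Protocol article*

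**What the plan says.** **Productivity loss is costed.** The Health Economic Evaluation section plans "a cost-effectiveness analysis (CEA) and a cost-utility analysis from a societal perspective" and lists disability to work among the costs. On valuation it says "Productivity loss due to disability to work is calculated based on the human capital approach". The research questions at the end of the Introduction ask whether the intervention affects indirect costs.

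**When work status is measured.** Table 1 marks each item as T0 only or as T0 and T1. "Employment status (eg, full time or part time or unemployed"), "Working hours per week", occupation, income level and average net monthly income are T0 only. So are occupational group and the self-employed or employed item. The only item on the work situation marked T0 and T1 asks about changes at work due to the pandemic.

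**When sick leave is measured.** Secondary Outcomes asks about health care use "retrospectively for the previous 6 months" and ends the same sentence with equipment and membership costs "as well as sick leave days". Table 2 has a days item, "Please indicate how many days in total", whose subject is not stated, followed by "If your sick leave has been for more than 6 months, please indicate how many days you have been on sick leave". Both are asked at T0 and T1.

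**The concern.** The human capital approach values working time lost. To apply it at T1, one needs to know whether the person is in work, for how many hours and, if individual earnings are used, at what wage. The schedule provides these facts only as they stood at baseline, during the pandemic. A person who stopped working because of illness after T0 may have no sick leave to report, because sick leave presupposes a job. In the data this person would look the same as a healthy worker or a new retiree with no absence. These states represent different amounts of lost work.

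At stake is the answer to the indirect-cost question, and one component of the incremental cost in both the cost-effectiveness and the cost-utility ratio. The primary step outcome is not affected.

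**Working it through.** The article gives no figure for sick-leave days, exits from work or cost per day, so there is nothing to reproduce. The check is of the item schedule, with two small illustrations.

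**1. Age of the work data at T1.** Baseline ran from the end of May 2021 to the end of March 2022 (Recruitment). Follow-up is planned from May to September 2023 (Results).
- Shortest gap: end of March 2022 to the start of May 2023 = 13 months.
- Longest gap: end of May 2021 to the end of September 2023 = 28 months.

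**2. What T1 can show about work.**

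| Information needed | T0 | T1 |
|---|---|---|
| Employment status | yes | no |
| Working hours | yes | no |
| Occupation, self-employment | yes | no |
| Income | yes | no |
| Pandemic-related changes at work | yes | yes |
| Sick-leave days | yes | yes |

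Two other sets of items do not fill the gap. The activity questionnaire is repeated at T1, but its work block covers paid and unpaid work together, so it does not establish employment. Chronic illness and diagnoses are T0 only, so they cannot identify a health-related exit after T0.

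**3. Reading a T1 answer of zero sick-leave days.** It fits three states: (a) working and not absent, (b) retired or otherwise not working for reasons unrelated to health, (c) out of work through illness. No scheduled T1 item separates them in general. An exit caused by the pandemic might show in the COVID-19 item; one caused by illness need not.

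**4. Scale of missed exits (assumed shares).** Suppose a share p of participants left work through illness, were out for the whole 6-month window of 182.5 days, and were given no cost. The mean calendar days missed per participant would be p × 182.5:
- p = 1%: 1.8 days
- p = 2%: 3.7 days
- p = 5%: 9.1 days

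The article supplies neither p nor a value per day. In the first draw, 500 of the 2,500 people sampled per city were aged 56 to 65. Exits by retirement or illness are plausible at that age, but how many occurred is unknown.

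**5. Secondary check: sick leave over 6 months.** If d days were entered uncapped against a 182.5-day window, the ratio to in-window days would be d / 182.5:
- d = 200: 1.10
- d = 270: 1.48
- d = 365: 2.00

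If the days are limited to the window, the ratio is 1. If they are uncapped but not scaled up, any d up to 365 stays within the 1-year horizon in the research questions.

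**The case against.** The strongest reply is that the article condenses a fuller plan. Capping, scaling, wage base and the work status to be applied are costing rules that usually sit in a health economic analysis plan, which is not shown. This stands, and it disposes of two stronger readings.

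- A reader might infer that long absences are overcounted. The article does not say that days beyond 6 months are used uncapped. The over-6-months question is a separate item, so these cases are identified and can be truncated at analysis. Table 2 is also abbreviated, so the item's true reference period cannot be judged.
- A reader might infer that exits from work are costed at zero, or that T1 days are valued on outdated data. No rule says either. With a standard cost per day, baseline income would not enter. Applying baseline status to reported days could equally overstate cost, for instance for someone who has since cut their hours.

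It can also be said that the same items and timing apply in both cities, so a biased ratio needs the error to differ between them. This stands too: no such difference can be shown. The design does not exclude one, because the cities are not randomised and weighting on baseline covariates does not correct changes in work after T0.

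What the reply does not reach is data collection. The tables fix timing item by item, and a later costing rule cannot recover T1 work status that was never asked.

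**Conclusion.** The point holds in a narrow form. Productivity loss is a stated cost component and indirect costs are a stated question, but general work status is measured once, 13 to 28 months before T1. A T1 report of no sick leave is therefore ambiguous, and health-related exits after T0 may be missed. This rests on the T0 and T1 markings in Tables 1 and 2 being complete.

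Neither the direction nor the size of any effect on the two ratios can be determined from the document, and no bias between cities is shown. The day counts above are illustrations under assumed shares. Euro amounts would need a unit cost and a case mix that the article does not give.

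The mismatch between the 6-month recall and the unlimited item for longer sick leave is a secondary remark, since it can be handled at analysis. The matter is confined to the economic evaluation.

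**What to change.** Before the T1 interviews start in May 2023, mark the existing items on employment status, working hours and income as T0 and T1, and add one item on the reason for leaving work (illness, retirement, other). State in the Health Economic Evaluation section that T1 productivity loss is based on T1 work status. Keep the baseline values, including household income, for the propensity weighting, because T1 work status arises after the intervention begins.

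For the secondary remark, add that sick-leave days are limited to the costing window at T0 and T1.

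The cost is three or four short items, about one extra minute in a 1-hour telephone interview, and two sentences of text. Once T1 is complete, the missing work status could be obtained only by recontacting participants.

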### Statistical Analyses

We will use the propensity score method for statistical analysis to allow for a nonrandomized design of the study. Specifically, the primary outcome will be estimated in a weighted 2-group comparison (intervention: yes vs no). For weighting, we will use matching weights [31] that are derived from a propensity score model for the intervention effect and an exhaustive list of covariates (Multimedia Appendix 2). The analysis will be blinded for the intervention effect and performed according to the intention-to-treat principle; missing values will be replaced via multiple imputation.

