	**Modified version of questionnaire of Chernyak et al [42]**			
		Purchases of equipment to promote your fitness, health and well-being (past 6 months)	T_0_, T_1_	

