	**EQ-5D-5L [44]**			
		Perceived health (eg, mobility, pain or physical discomfort, or anxiety)	T_0_, T_1_	

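### The economic propensity model omits baseline EQ-5D-5L utility and prior resource use, so city differences that its five covariates do not explain would count as intervention effects

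*Protocol article*

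**What the plan says.** The Health Economic Evaluation section states the purpose of the weighting ("To make the random samples from the intervention and control region comparable, propensity score matching in the form of a weighted regression model will be"); this step comes once missing values have been imputed, separately in each completed data set. The covariates follow in one sentence: "Covariates used for the matching will be the number of steps taken at baseline, age, gender, level of education, and household income". The list has no opening for further variables and no pointer to an appendix.

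The economic outcomes are defined in the same section. The ICER is the cost per extra person reaching 10,000 steps a day, with the step outcome taken from the pedometer. The ICUR is the cost per QALY gained, and "QALYs will be calculated based on the EQ-5D-5L [44"]. A capability comparison based on ICECAP-A is also planned. Costs cover the intervention, health care use, spending related to physical activity, and inability to work.

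Table 2 lists these items at both T0 and T1:
- EQ-5D-5L: "Perceived health (eg, mobility, pain or physical discomfort, or anxiety").
- Health care use over six months, for example "Have you seen a physician in the last 6 months" and "Have you been hospitalized for inpatient treatment in the last 6 months", with therapist contacts, rehabilitation and days of sick leave.
- Spending: "Purchases of equipment to promote your fitness, health and well-being (past 6 months").
- The five ICECAP-A items.

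The section names generalized linear models for costs and for the step outcome. It does not say which regressors they contain.

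**The concern.** The design has one intervention city and one control city, without randomisation, so comparability rests on the variables in the weights. For the step outcome the list includes its own baseline value. For QALYs and costs it does not, although the corresponding T0 values exist and were collected before the intervention began in April 2022.

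Two residents with the same steps, age, gender, education and income can still differ in health and in use of care. If such differences are distributed unevenly between the two sets of districts, the weights do not remove them. An advantage that one city already had would then appear as QALYs gained or costs saved, or as the reverse.

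**Working it through.** The plan gives no figure to reproduce here. The check has two parts: which quantities are exposed, and how large the effect could be on stated assumptions.

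**Exposure of each ratio**

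| Quantity | Baseline value collected at T0 | In the economic propensity list |
|---|---|---|
| Reaching 10,000 steps (ICER denominator) | yes, pedometer steps | yes |
| Costs (numerator of ICER and ICUR) | yes, six-month resource use, sick leave, purchases | no |
| QALYs (ICUR denominator) | yes, EQ-5D-5L | no |
| Capability well-being | yes, ICECAP-A | no |

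So the ICER is exposed through its numerator, and the ICUR through both parts.

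**QALY illustration**

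Assumptions, none of them in the article: QALY over one year = (U0 + U1)/2; true effect zero; d = utility gap at T0 that remains after weighting; r = T0-T1 correlation, so that the gap expected at T1 is r × d.

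Spurious QALY difference = d × (0.5 + 0.5r). For d = 0.02:
- r = 0.5: 0.02 × 0.75 = 0.015
- r = 0.6: 0.02 × 0.80 = 0.016
- r = 0.7: 0.02 × 0.85 = 0.017
- stable gap, with no shrinkage at T1: 0.02 × 1 = 0.020

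The result scales with d.

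**How much the five covariates might remove**

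Assume a raw city gap of 0.2 SD, a utility SD of 0.15 (raw gap 0.2 × 0.15 = 0.03), a follow-up cost SD of 2000 currency units, r from 0.5 to 0.7, and listed covariates that explain a share R² of 5% to 30% of the baseline variance. A single score stands in for the five covariates.

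*Listed covariates equal in the two cities.* The weights have nothing to act on and the full gap stays.
- QALY: 0.03 × 0.75 = 0.0225 to 0.03 × 0.85 = 0.0255.
- Cost: 0.2 × 0.5 × 2000 = 200 to 0.2 × 0.7 × 2000 = 280 units.

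*Listed covariates also 0.2 SD apart.* The part they carry is removed, and the residual gap is 0.2 × (1 − √R²) SD.
- R² = 0.05: 0.155 SD, or 0.0233 in utility; QALY 0.0175 to 0.0198; cost 155 to 217 units.
- R² = 0.30: 0.090 SD, or 0.0136 in utility; QALY 0.0102 to 0.0115; cost 91 to 127 units.

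A simulation of matching weights with 400,000 persons per scenario agrees. Without the baseline outcome in the propensity model, the spurious QALY difference was 0.022 to 0.026 in the first case and 0.011 to 0.020 in the second. The spurious cost difference was about 190 to 280 and 90 to 215 units. With the baseline outcome added, the QALY difference stayed within 0.0003 of zero and the cost difference within about 7 units.

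That near-zero result depends on the assumption that the cities differ at T1 only through T0. If the gap is stable, regression on baseline leaves part of it: with d = 0.02 and r = 0.6, 0.5 × 0.02 × (1 − 0.6) = 0.004, against 0.020 unadjusted.

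**The case against.** Several points on the other side stand.

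- A reader might infer that earlier city differences pass whole into both ratios. They do not. Age, gender, education and income remove the part they explain, districts were selected using a socio-spatial deprivation index, and the ICER's effect measure is balanced on baseline steps.
- A reader might infer that the economic analysis contradicts the primary one, whose weights are "derived from a propensity score model for the intervention effect and an exhaustive list of covariates". That is not shown. The list is in Multimedia Appendix 2, which is not available here, and it is stated for the number of steps, whereas the economic outcome is reaching 10,000 steps. For the same reason that list cannot be recommended as a replacement.
- The outcome models are named without regressors, and no separate QALY regression is described. Baseline terms could stand in a fuller analysis plan. The stated fault is therefore confined to the propensity list; the article names nothing that makes up for the omission, but it does not exclude it either.
- Every magnitude above is assumed. A reversed sign of the ICUR is conceivable but cannot be calculated from the article.
- More covariates can cost overlap and effective sample size.

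None of this gives a reason to leave the baseline values of the economic outcomes out of a list that is otherwise fixed.

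**Conclusion.** The point holds in a limited form. The economic propensity list is closed, and it omits baseline utility and prior resource use, which are available and precede the intervention. The part of any city difference in these that the five covariates leave unexplained would count as an intervention effect in the cost numerator of the ICER and in both parts of the ICUR.

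Size and direction are unknown. On the assumptions shown, a residual utility gap of 0.02 means 0.015 to 0.017 QALY, and 0.02 if the gap is stable. The matter concerns the accompanying economic evaluation; the primary step comparison is not affected.

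**What to change.** Amend the covariate sentence in the Health Economic Evaluation section in one or both of these ways:

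- Add baseline EQ-5D-5L utility and baseline six-month costs, or the resource use, sick leave and purchases from which they are valued, to the economic propensity model. For the capability comparison, add baseline ICECAP-A.
- State that the weighted QALY and cost regressions include the baseline value of their own outcome.

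The T0 interview already holds every variable, so the change is one of wording and analysis. The possible cost is a slight loss of overlap or effective sample size in the weights. Reporting baseline utility and resource use by city, before and after weighting, would show how much imbalance the weights remove and what remains.

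### The economic evaluation gives its yes/no step outcome two incompatible models, names none for incremental QALYs, and states no adjustment of QALYs for baseline utility

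*Protocol article*

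**What the plan says.** All of this stands in the protocol article, Methods, Health Economic Evaluation, unless another place is named.

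- Two ratios are planned. The cost-effectiveness ratio (ICER) is defined as "additional costs per additional person walking 10,000 steps/day". For utility, an "incremental cost-utility ratio (ICUR; additional cost for an additional QALY gained) will be determined".
- On deriving utility: "QALYs will be calculated based on the EQ-5D-5L", with a German tariff.
- First modelling sentence: "Mean incremental costs and the mean incremental outcome of the CEA will be estimated by a using a Generalized Linear Model with gamma distribution" and a log link.
- Second modelling sentence: "To estimate the mean incremental outcome of the CEA (an additional person who walks 10,000 steps/day), a Generalized Linear Model with binomial distribution" and a logit link.
- On uncertainty: "Bootstrap procedures will be used to calculate 95% significance intervals for the ICER and ICUR", together with cost-effectiveness and cost-utility planes.
- To make the cities comparable, a propensity-score-weighted regression is run in each imputed data set. Its matching covariates are baseline steps, age, gender, education and household income.
- Table 2 (Secondary Outcomes) shows the EQ-5D-5L at both baseline and follow-up.

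**The concern.** The two modelling sentences use the same name for one quantity and give it different distributions and links. The second defines that quantity as a yes/no outcome, for which a gamma distribution is not a possible model. The incremental QALYs, without which the cost-utility ratio cannot be formed, appear in neither sentence.

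The article does not merely leave detail to a fuller plan here. It states distribution and link, and what it states conflicts. Both ratios answer a research question listed at the end of the Introduction. An analyst following the text would have to choose a model for one denominator and invent one for the other after the data are in, and the Discussion already expects a cost-effective result.

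The covariate list matters for the same denominator. The cities are not randomised, and QALYs depend directly on where each person's utility starts. If baseline utility is neither a matching covariate nor a term in a stated QALY model, a starting difference between Duesseldorf and Wuppertal can be read as an effect of the intervention.

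**Working it through.** The article reports no figure for these models, so there is nothing to reproduce. The check sets what is needed beside what is provided.

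**1. Quantities and models**

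| Increment | Used in | First sentence | Second sentence |
|---|---|---|---|
| Costs | both numerators | gamma, log | – |
| Proportion walking 10,000 steps/day | ICER denominator | gamma, log | binomial, logit |
| QALYs | ICUR denominator | – | – |

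One row has two models and one has none.

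**2. Are the two models compatible?** The gamma distribution is continuous on positive values with variance proportional to μ². A 0/1 variable has variance μ(1 − μ). With weights w, the estimating equations are:

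- gamma-log: Σ w x (y − μ)/μ = 0
- binomial-logit: Σ w x (y − μ) = 0

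If city is the only regressor, both are solved by the weighted proportion in each city, so the point estimates coincide. Once covariates enter, the equations differ, and the log link can give fitted proportions above 1. The conflict is therefore certain in the text, while its numerical effect depends on a regression content that the article does not give.

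**3. Does one slip explain both gaps?** If the first sentence is read as costs and the outcome of the cost-utility analysis, the table fills exactly: costs and QALYs gamma-log, step outcome binomial-logit. That is the likeliest intention. But the abbreviation list expands CEA only as cost-effectiveness analysis, and the article has no abbreviation for the cost-utility analysis, so nothing on the page confirms it. On this reading QALYs would receive a right-skewed, strictly positive distribution, although in a general-population sample they tend to bunch near their upper limit.

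**4. Baseline utility.** The matching list has five items: baseline steps, age, gender, education, household income. Utility is not among them, although Table 2 shows that it is collected at baseline. To see the consequence, assume (the article does not state it) that QALYs are the area under a straight line between the two assessments over one year:

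- QALY = (u0 + u1)/2.
- Let the cities differ by d at baseline after weighting, let a share ρ of that difference persist at follow-up, and let the intervention have no effect.
- Apparent QALY gain = (d + ρd)/2 = d(1 + ρ)/2.
- With ρ = 0 this is d/2; with ρ = 1 it is d.

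The documents give no value for d, so only the form of the bias can be stated.

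**5. Zero costs.** The gamma-log equation contains y itself and not log y, so it accepts y = 0. Simulated costs for 319 people per group (the stated 638 divided by 2), with 5% to 30% zeros assumed, gave fits that converged and matched the raw mean difference each time. In one run with 36 zeros in control and none in intervention, both were 89.73. Only the log-likelihood became infinite. With no per-head intervention cost and 20% zeros assumed, zeros fell in both groups (63 and 64).

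**The case against.** The strongest defence is that this is one misplaced phrase. Binomial-logit suits the step outcome, gamma-log is a common choice for skewed costs, and replacing the first mention of the cost-effectiveness outcome by the cost-utility outcome removes both the double model and the missing one. This lowers the seriousness. It does not remove the need to correct the text, since a reader cannot tell from the article which sentence governs.

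A second defence is that the full plan may include baseline utility in its QALY model, or that the longer covariate list in Multimedia Appendix 2 may contain it. That list belongs to the propensity model described under Statistical Analyses. The economic section states its own shorter list, and utility is not on it. What stands of this defence is that the gap is shown for the article only.

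A reader might go further and infer that a gamma model cannot handle zero costs, that zeros arise only in Wuppertal, and that the control mean would be inflated. The documents do not support this. The gamma-log estimating equations take zeros. The article states intention-to-treat analysis and no deletion of zero-cost participants. It counts "costs related to the development and provision of the intervention" among the costs but does not say that a share is charged to each Duesseldorf participant. It also lists patient time as a cost, which could make control costs positive, though its place in the base case is unclear because it appears again as a sensitivity analysis. Any inflation figure would rest on allocation and deletion rules that the article does not contain.

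A reader might also object that log and logit coefficients are ratios while the ICER and ICUR need differences. The article names mean increments as its targets, and converting to the natural scale is routine detail for the full plan.

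**Conclusion.** The point holds in limited form. The modelling text contradicts itself on the yes/no step outcome and leaves incremental QALYs without a model; both follow from the wording alone and need no assumption. As the article stands, the QALY comparison is also not adjusted for baseline utility. Under the linear-interpolation assumption, a residual baseline difference d would appear as a QALY difference of between d/2 and d for persistence between none and full.

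No numerical size can be attached. For the step outcome the effect on the point estimate would be nil if city is the only regressor, and is unknown otherwise. For QALYs it depends on d, which the documents do not give.

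The matter concerns an accompanying economic evaluation. The primary outcome, pedometer steps, has its own analysis and is untouched. The correction should be made before the economic results are called prespecified, but it ranks below changes on which the trial's main conclusion depends.

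**What to change.** Rewrite the modelling paragraph of the Health Economic Evaluation so that each increment has one model:

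- **Costs:** gamma GLM with log link, for costs only, with a note that zero-cost participants stay in the model.
- **Step outcome:** binomial GLM with logit link, for this outcome only.
- **QALYs:** a weighted regression, for example linear, with baseline EQ-5D-5L utility as a covariate.

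All three should run within the multiple imputation, weighting and bootstrap already planned, so that each ratio's numerator and denominator come from the same resamples.

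The cost is a change of wording in the analysis plan and a small change in the analysis code. No new data are needed, because the EQ-5D-5L is already collected at baseline, and neither the sample size nor the primary analysis changes.
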